### Data and statistical analysis

2.5

Statistical analysis will be carried out using SPSS 25.0 software (SPSS Inc., Chicago, Illinois) and Stata 14.3. Comparisons of characteristics of patients will be performed using Chi-squared tests for qualitative variables and Student’s t or Mann-Whitney tests as appropriate. Confidence intervals (CI) for proportions (sensitivity, specificity, accuracy) will be calculated using the Wilson Score method. With the last iteration of the FFR-CT software, the per-patient sensitivity and specificity were 86% (95% CI: 77% to 92%) and 79% (95% CI: 72% to 84%) [9]. In the recent VERDICT trial based on NSTEMI patients [10], 12% had 3 vessel disease, 23% 2 vessel disease (which included left main), 34%, 1 vessel disease, 30% nothing, Thus, out of 100 patients with 300 coronaries, we expect 106 (i.e. 36 + 46 + 34) vessels with a stenosis. Based on the FAMOUS NSTEMI trial [11], 60% of invasive FFR measurements of these stenoses were significant [12]. Thus, with a standard error of 0.05, and for a power of 80%, 204 patients will be required. However, some of the CT will not be suitable for analysis and some patients will have to be excluded. Therefore, we plan to include 250 patients. Of note, these number is also in line with the literature investigating the accuracy of FFR-CT versus FFR in patients with stable coronary artery disease [9], [13]. For the treatment decision based on the various methods, McNemar's test will be used.

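### The sample-size section prints 106 expected stenosed vessels per 100 patients, but its own terms sum to 116

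*Protocol article*

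**What the plan says.** All the relevant text is in section 2.5 of the Protocol article (Data and statistical analysis). It takes per-patient FFR-CT sensitivity and specificity of 86% and 79% from a study of the latest software. It then takes the extent of disease from a trial in NSTEMI patients: "12% had 3 vessel disease, 23% 2 vessel disease (which included left main), 34%, 1 vessel disease, 30% nothing". From this it builds a vessel count, "out of 100 patients with 300 coronaries": "we expect 106 (i.e. 36 + 46 + 34) vessels with a stenosis". A second trial supplies the share that is functionally significant: "60% of invasive FFR measurements of these stenoses were significant". The required number is given as a consequence: "with a standard error of 0.05, and for a power of 80%, 204 patients will be required". An allowance for unsuitable CT scans and exclusions follows: "Therefore, we plan to include 250 patients".

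The section gives no formula, significance level, null value or target difference. It does not show where the vessel count enters the 204.

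**The concern.** The total and the sum in brackets stand in the same sentence and disagree. The count is a planning input: the 60% is applied to it, and the required number is introduced as following from that chain. A reader who takes 106 at face value will expect too few FFR-positive vessels. These form the denominator for vessel-level sensitivity of FFR-CT, and sensitivity is among the co-primary endpoints in section 2.3. The expected precision would be understated, and nobody can check the 204 while it is unclear which count lies behind it.

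**Working it through.** **Inputs (all from section 2.5).** Three-vessel disease 12%, two-vessel 23%, one-vessel 34%, none 30%; 300 vessels per 100 patients; 60% of stenoses FFR-positive; sensitivity 0.86, specificity 0.79; 204 required, 250 planned.

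**Step 1: the vessel count.** 12 × 3 = 36, 23 × 2 = 46, 34 × 1 = 34. Each term matches the one printed. 36 + 46 + 34 = 116, so the printed 106 is not reproduced. Rounding does not explain the gap. The four percentages sum to 99, but if each of the three were off by half a point the count would move by at most 0.5 × (3 + 2 + 1) = 3, giving 113 to 119.

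**Step 2: what follows directly.**

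| Quantity | With 106 | With 116 |
|---|---|---|
| FFR-positive vessels per 100 patients (× 0.60) | 63.6 | 69.6 |
| Share of 300 vessels | 21.2% | 23.2% |
| FFR-positive vessels in 204 patients | 129.7 | 142.0 |
| FFR-positive vessels in 250 patients | 159.0 | 174.0 |

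The correct count is 9.4% above the printed one (116/106 = 1.094).

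**Step 3: can the 204 be traced to either count?** The stated inputs do not determine it. Taken literally, a standard error of 0.05 for sensitivity needs 0.86 × 0.14 / 0.05² = 48.2 FFR-positive vessels. That is 48.2 / 0.636 = 75.7, so 76 patients with 106, or 48.2 / 0.696 = 69.2, so 70 patients with 116. Neither is near 204. Trying other formulas gives matches from both counts:

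- From 106: 1.64² × 0.86 × 0.14 / 0.05² = 129.5, and 129.5 / 0.636 = 203.7, so 204. The same formula with 0.696 gives 186.1. With z = 1.645 instead of 1.64, the 106 version gives 204.9, so 205.
- From 116: (1.96 + 0.8416)² × 0.86 × 0.14 / 0.10² = 94.5, and 94.5 / 0.464 = 203.67, so 204. Here 0.464 is the number of FFR-negative stenoses per patient (1.16 × 0.40).
- From 116: 1.28² × 0.86 × 0.14 / 0.05² = 78.9, and 78.9 / (1.16/3) = 204.07.

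These matches came from trying many combinations of z, margin and denominator. None is shown to be the authors' method.

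**Step 4: effect if 106 was used.** Suppose the required number is inversely proportional to vessels per patient. Then 204 × 106/116 = 186.4, so about 187. If 204 was already built on 116, it does not change.

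**Step 5: expected precision.** The standard error of vessel-level sensitivity is √(0.86 × 0.14 / number of FFR-positive vessels). The standard error of specificity among stenosed vessels is √(0.79 × 0.21 / number of FFR-negative stenoses).

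| Patients analysed | Sensitivity SE, 106 | Sensitivity SE, 116 | Specificity SE, 106 | Specificity SE, 116 |
|---|---|---|---|---|
| 204 | 0.0305 | 0.0291 | 0.0438 | 0.0419 |
| 250 | 0.0275 | 0.0263 | 0.0396 | 0.0378 |

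These figures apply the cited per-patient accuracy to vessels and treat vessels within a patient as independent. Both are simplifying assumptions.

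**The case against.** The best case for leaving this alone is that 106 may be a one-digit misprint of 116, with the calculation done correctly. The article is a condensed account, and the full calculation may sit elsewhere. Even if the slip did enter the calculation, more stenosed vessels per patient means fewer patients needed, so it errs on the safe side. Enrolment, endpoints and analysis would not change.

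Most of this stands, and it limits the point to a minor one. It does not remove it: the sum is wrong on the page, and no unseen document can make those three terms total 106. The remark that two-vessel disease included left main does not help either, because the bracket itself prints 46.

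A reader might go further and infer that the sample size rests on the wrong input, since 204 can be reached from 106. The document does not support that. The 106 route needs z cut to 1.64, a 90% confidence level that the section never mentions, no power term although 80% power is stated, and the standard error read as a half-width. It also divides a per-patient sensitivity by a per-vessel count. Formulas fitted just as freely reach 204 from 116, one of them with a power term, although that one pairs sensitivity with FFR-negative vessels. A match found in this way does not identify the input. Nor does the slip suggest that the trial is too small.

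**Conclusion.** The arithmetic error is certain and rests only on the article's own figures: the expected count is 116 stenosed vessels per 100 patients, not 106. The number of FFR-positive vessels is therefore 69.6 rather than 63.6 per 100 patients, so the printed chain understates it by 6.0/69.6 = 8.6%.

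Whether the slip reached the 204 cannot be determined from the document. If it did, and if the requirement scales inversely with vessels per patient, about 187 patients would be needed. Both 204 and 250 exceed that, so 250 remains sufficient on this account. The gain in expected precision is small: at 250 patients the standard error of sensitivity falls from 0.0275 to 0.0263 under the assumptions in the working. Severity is minor.

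**What to change.** In section 2.5, replace 106 with 116. Carry the corrected count through, giving 69.6 FFR-positive and 46.4 FFR-negative stenosed vessels per 100 patients. Recompute the required number from it, print the formula, and say which count produced 204. Restate the expected precision at the planned enrolment, which stays at 250, and at the number expected to be analysable.

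The cost is one corrected figure and one recalculated line. Recruitment, procedures, endpoints and analysis are unaffected.

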### Hypothesis and study endpoints

2.3

The hypothesis to be tested is that FFR-CT might have an interest in three aspects of the management of high-risk NSTE-ACS patients:(1)FFR-CT discriminates those without any significant lesions defined by a negative invasive FFR value (>0.80) among all lesions with ≥30% diameter stenosis by invasive angiographic evaluation.(2)FFR-CT discriminates those with a significant lesion (defined by a positive invasive FFR (≤0.80).(3)When a clear culprit-lesion is evident (i.e. sub-occlusive vessel and ECG changes in the same territory), FFR-CT helps for the management of the non-culprit lesions (good correlation compared to invasive FFR).

Co-primary endpoints will be negative predictive value of coronary CT angiography and FFR-CT as compared to angiography with FFR and accuracy, sensitivity, specificity and positive predictive value of FFR-CT as compared to angiography with FFR.

Secondary endpoints will be (1) correlation of FFR-CT as compared to invasive FFR in lesions with at least a 30% stenosis, (2) negative predictive value of coronary CT as compared to angiography, (3) accuracy, sensibility, specificity and positive predictive value of coronary CT as compared to angiography, (4) accuracy, sensibility, specificity, negative predictive value and positive predictive value of FFRangio™ as compared to angiography (5) a priori treatment decision after angiography versus treatment decision according to invasive FFR, (6) a priori treatment decision after angiography versus treatment decision according to FFRangio™, (7) a priori treatment decision after angiography versus treatment decision according to FFR-CT, (8) natural history of deferred lesions according to invasive FFR, FFR-CT, CT and FFRangio™ in term of MACE

The following safety endpoints will be systematically recorded: Radiation dose received per patient (mSv), contrast media dose received per patient (ml), incidence of acute kidney failure defined as an increase of >1.5x the baseline creatinine value 3 days after the coronary-CT, incidence of vascular complications related to the coronary angiogram, incidence of stroke and incidence of major cardiac adverse events (MACE, composite outcome including cardiovascular death, myocardial infraction, and urgent revascularization).

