To date, there is no simple non-invasive tool that might be applied on these high-risk patients as all the emerging techniques such as coronary CT or FFR-CT have only been studied in low-risk patients. Moreover, in a population of patients with recent STEMI and multivessel disease, FFR-CT has been shown to have only moderate accuracy in the evaluation of non-culprit lesions [20]. This fact might be explained by a smaller vessel volume and lower volume to mass ratio in the immediate post-STEMI period. It is still unknown if the same will apply in high-risk NSTE-ACS. In case of positive results of the present study, the next step would be to design a randomized trial assessing outcomes for patients assigned to one strategy or another, with a potential final perspective to use FFR-CT as a gatekeeper technique very early in the management of high-risk NSTE-ACS patients. This strategy would allow to classify these latter into 3 groups: those with non-coronary etiology, those with coronary etiology with an anatomy suitable for PCI, and those with complex multi-vessel disease needing CABG surgery. In the latter category, early identification might allow to avoid use of dual antiplatelet therapy and thus allowing for faster surgery with a lower bleeding risk.

Accordingly, the interest goes beyond its scientific aspects as the project might benefit directly to numerous patients, and as a public-health impact might expected with simpler management of this broad population. Finally, in times of growing health expenditures, this simple and non-invasive technique might contribute to cost control as it might spare numerous expensive procedures.

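### The stated standard error of 0.05 does not give 204 patients for any FFR-CT co-primary measure, and the stated 80% power has no numerical null or goal behind it

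*Protocol article*

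**What the plan says.** Section 2.5 (Data and statistical analysis) builds the sample size from these inputs:

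- FFR-CT performance from a study in stable disease: "the per-patient sensitivity and specificity were 86% (95% CI: 77% to 92%) and 79% (95% CI: 72% to 84%)".
- Extent of disease from an NSTEMI trial: "12% had 3 vessel disease, 23% 2 vessel disease (which included left main), 34%, 1 vessel disease, 30% nothing".
- A vessel count derived from that: "out of 100 patients with 300 coronaries, we expect 106 (i.e. 36 + 46 + 34) vessels with a stenosis".
- The share of stenoses that are FFR-positive: "60% of invasive FFR measurements of these stenoses were significant".

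It then concludes that "with a standard error of 0.05, and for a power of 80%, 204 patients will be required" and, after an allowance for unusable scans and exclusions, "Therefore, we plan to include 250 patients".

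The same section plans Wilson confidence intervals for sensitivity, specificity and accuracy. The only test it names for an endpoint is McNemar's, for treatment decisions, which are secondary.

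Section 2.3 says "Co-primary endpoints will be negative predictive value of coronary CT angiography and FFR-CT as compared to angiography with FFR", and adds the accuracy, sensitivity, specificity and positive predictive value of FFR-CT. Its three hypotheses are verbal (FFR-CT discriminates, or helps). None carries a minimum value.

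**The concern.** A standard error and a power are different specifications. A standard error fixes the precision of an estimate. A power is the chance of rejecting a stated null value at a stated alpha. The paragraph gives both for one number, names no measure, unit, alpha or null, and mixes per-patient accuracy figures with a per-vessel count without saying how they combine. A reader cannot tell what 204 was sized for.

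This matters because the trial asks whether FFR-CT is good enough to spare some patients angiography, and NPV is the first co-primary measure named. Someone told that the study has 80% power will assume that it can confirm some level of performance. The article defines no such level. The precision it can offer on NPV is not stated and does not follow from the figures given.

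**Working it through.** **Inputs** (section 2.5): sensitivity 0.86; specificity 0.79; 12%, 23% and 34% of patients with 3, 2 and 1 diseased vessels; 60% of stenoses FFR-positive; 0.05; 80% power; 204.

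**Vessel count.** 12×3 + 23×2 + 34×1 = 36 + 46 + 34 = 116 per 100 patients, not 106. FFR-positive vessels per patient are 1.06×0.60 = 0.636 as stated, or 1.16×0.60 = 0.696 corrected. FFR-negative stenoses are 0.424 or 0.464.

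**Per-patient prevalence.** The article gives no figure, so I bracket it.
- All stenoses in a patient share one FFR status: 0.69×0.60 = 0.414.
- Stenoses are independent: 0.34×0.60 + 0.23×(1−0.4²) + 0.12×(1−0.4³) = 0.510.

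**Does a standard error of 0.05 give 204?** Units needed are p(1−p)/0.05².
- Sensitivity: 0.86×0.14/0.0025 = 48.2 FFR-positive units.
- Specificity: 0.79×0.21/0.0025 = 66.4 FFR-negative units.

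Dividing by the relevant units per patient gives the patients required:

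| FFR-CT measure | Per patient (prevalence 41–51%) | Per vessel, 106 | Per vessel, 116 |
|---|---|---|---|
| Sensitivity | 94–116 | 76 | 70 |
| Specificity | 113–135 | 157 | 144 |
| NPV | 76–115 | 157 | 144 |
| PPV | 114–159 | 76 | 70 |
| Accuracy | 58–59 | 53 | 49 |

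Nothing reaches 204.

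**Does 80% power give 204?** No null is stated, so this cannot be computed. As an illustration only, I borrow the quoted lower confidence limits (0.77 and 0.72) as nulls, with alpha 0.05, one- or two-sided, per patient or per vessel. The requirement then runs from 172 to 720 patients, and no variant lands on 204.

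**What does come close?** Reading 0.05 as a confidence-interval half-width, per vessel:
- 90% interval for sensitivity: 1.64²×0.1204/0.0025 = 129.5; divided by 0.636 = 203.7 (z = 1.645 gives 204.9).
- 95% interval for accuracy: 0.60×0.86 + 0.40×0.79 = 0.832; 1.96²×0.832×0.168/0.0025 = 214.8; divided by 1.06 = 202.6.

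Both need the misadded 106. With 116 they fall to 186–187 and 185. Neither involves power.

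**What 204 evaluable patients deliver, per patient, 95% Wilson:**
- Sensitivity: 84 to 104 FFR-positive patients, half-width 0.074 to 0.067.
- Specificity: 120 to 100 FFR-negative patients, half-width 0.072 to 0.079.
- NPV = 0.79(1−p)/[0.79(1−p) + 0.14p]. At p = 0.414 it is 0.889 on about 106 test-negatives, interval 0.81–0.94. At p = 0.510 it is 0.845 on about 94, interval 0.76–0.90. Half-width 0.060 to 0.073.

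**The case against.** The strongest reply is that the error is one of wording and on the safe side. With 204 patients the per-patient standard errors are about 0.034 to 0.038 for sensitivity and 0.037 to 0.041 for specificity, better than the stated 0.05. That stands: the standard error discrepancy is no reason to recruit more.

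A second reply is that 0.05 beside a power of 80% may be a mislabelled alpha. Sensitivity 0.86 against 0.76, two-sided, needs 127.5 FFR-positive vessels, and 127.5/0.636 = 200.5 patients. This is possible, but the 10-point margin appears nowhere and the result is not 204.

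A third concerns the NPV of coronary CT itself. With the 94% sensitivity and 34% specificity quoted in section 3.1, the same formula gives 0.0986/0.0025/0.224 = 176 patients at 41% prevalence and 0.1309/0.0025/0.197 = 265 (unrounded inputs) at 51%, a range that includes 204. The sizing paragraph uses neither CT figure, so this does not explain its number. It is why the point is confined to the FFR-CT measures.

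Stronger readings are tempting, and the document does not support them:
- That the trial lacks 80% power. Without a null, power is unsupported, not disproved. A goal and alpha may sit in the full protocol, which is not shown.
- That there is no hypothesis. Section 2.3 states three; what is absent is a number.
- That the authors used a 90% half-width and put a per-patient sensitivity on vessels treated as independent. That is one of several guessed routes to about 204. The text shows only that inputs of both kinds are listed.
- That a pass mark is owed because section 3.3 says "In case of positive results of the present study, the next step would be to design a randomized trial". This is Discussion text about a later study, not a decision rule. Section 3.2 presents the work as preliminary.

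**Conclusion.** Wrong as written. A standard error of 0.05 on the paragraph's own inputs requires 49 to 159 patients, depending on FFR-CT measure, unit and vessel sum, and never 204. The 80% power refers to no stated null, goal or threshold test and cannot be verified. A mislabelled precision calculation is the likeliest origin, but two different ones fit and the text states neither.

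The size of the matter is in what readers will believe rather than in the number recruited: at the planning figures NPV would be estimated at about 0.84 to 0.89, with a 95% interval that could start at 0.76.

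This rests on three assumptions: that the stable-disease sensitivity and specificity carry over, that 60% of stenoses are FFR-positive, and that within-patient correlation lies between none and complete, which gives the 41% to 51% prevalence.

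**What to change.** Keep 250 enrolled and 204 evaluable. In section 2.5:

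1. Correct the vessel sum to 116.
2. Delete the standard error of 0.05 and the power of 80%.
3. Name the measure and the unit of analysis to which the sample size refers.
4. State the expected per-patient 95% precision with 204 evaluable patients: half-widths of about 7 points for sensitivity, 7 to 8 for specificity and 6 to 7 for NPV, with expected NPV about 0.84 to 0.89 (intervals about 0.76–0.90 to 0.81–0.94), and the prevalence range assumed. These figures use the vessel-disease distribution directly and do not depend on the sum in item 1.
5. Describe the study as estimation. If a numerical goal with its alpha already exists, state it instead and recompute the power at 204.

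The cost is the rewriting of one paragraph. No patients are added and the planned Wilson intervals stay as they are. Naming a single primary endpoint or setting a pass mark for NPV is a design choice on which statisticians may differ; it is optional and not part of this correction.

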### Ethics

2.6

This project has been approved in May 2019 by the Medical Ethical Committee from canton de VAUD (CER-VD). The trial is also registered on ClinicalTrials.gov (NCT04052763).

This research project will be conducted in accordance with the protocol, the Declaration of Helsinki, the principles of Good Clinical Practice, the Human Research Act (HRA) and the Human Research Ordinance (HRO) as well as other locally relevant regulations

## Discussion

3

### Study population

3.1

Coronary CT as an adjunctive diagnosis tool as already been studied in the past, but in different sub-populations. In *a meta*-analysis of 9 studies (n = 1349 patients), CT presented an overall high negative predictive value to exclude ACS in patients presenting to the ED with chest pain and suspected of having an ACS [14]. The sensitivity (95% CI) of CT for NSTE-ACS diagnosis was 95% (88–100) and specificity (95% CI) was 87% (83–92), yielding a negative likelihood ratio (95% CI) of 0.06 (0–0.14) and positive likelihood ratio (95% CI) of 7.4 (4.8–10). However, in these studies, patients were in low to intermediate chest pain risk category with normal initial cardiac biomarkers and none had evidence of ischemia on initial ECGs and a NSTE-ACS was subsequently diagnosed in 10% of patients only.

Different randomized controlled trials have tested CT (n = 1869 patients) vs. usual care (n = 1397) in the triage of low- to intermediate-risk patients presenting with acute chest pain to ED without signs of ischemia on ECG and/or inconclusive cardiac troponins. At a follow-up of 1–6 months, there were no deaths, and a meta-analysis demonstrated comparable outcomes with the two approaches (i.e. no difference in the incidence of MI, post- discharge ED visits or rehospitalizations) and showed that Multiple Detector Computed Tomography was associated with a reduction in ED costs and length of stay. However, none of these studies used high-sensitivity cardiac troponin assays which is now the standard of care [15], [16], [17], [18].

FFR-CT is a rising technology and different studies – focusing on patient with stable coronary artery disease – have validated its good accuracy compared to invasive FFR. Per-patient sensitivity and specificity (95% CI) to identify myocardial ischemia (positive FFR) were 86 (77–92) % and 79 (72–84) % for FFR-CT versus 94 (86–97) % and 34 (27–41%) % for coronary CT in a study involving 254 patients [9]. In another study based on 252 patients [13], which did not achieve its prespecified primary outcome goal for the level of per-patient diagnostic accuracy (73% only), use of non-invasive FFR-CT among stable patients with suspected or known coronary artery disease was associated with improved diagnostic accuracy and discrimination compared to CT alone for the diagnosis of hemodynamically significant stenosis with FFR.

